#### Materials and measures

##### Choice of measures

Materials from online databases (PsycTESTS, DMIDI) were selected based on psychometric quality, fitness for parental context, translation feasibility, and the significance of usage in a variety of international institutions. Due to the complexity of our proposed model, and to avoid dropout due to the length of the final battery, we have adapted certain instruments and developed questions to assess specific constructs.

Additionally, data about each country will be gathered from different national, international and scientific entities, such as the percentage of vaccinated children in a country (World Health Organization, 2017b), number of physicians per 1000 inhabitants (World Health Organization, 2017a), health system quality (GBD 2015 Healthcare Access and Quality Collaborators, 2017) and about the vaccination programme in each of the countries (obtained from the corresponding governmental communications).

For the measurement of different constructs to be homogenous, all continuous variables will be measured with 7-point Likert-type scales. This is because most of the instruments used in the study originally included this type of scale, and the number of points in Likert-type scales do not influence its metric properties (Contractor and Fox, 2011).

##### Sociodemographic list

The sociodemographic data to be gathered includes participants' country of residence, age, gender, education (based on European Qualifications framework), marital status, number of children, age of children, the adherence to the official vaccination schedule of the child in the corresponding country, and if the participant themselves adhered to said vaccination schedule (Appendix 1). Subjective Socioeconomic Status (sSES) will rely on the level of education, and on participant's self-report regarding the “difficulty of the household to make ends meet” (Eurostat, 2017).

##### Intention to vaccinate

We will measure parents' willingness to vaccinate their children by their reported intention to vaccinate when presented with the option. To measure this, a single item will be used: “Would you at this time vaccinate your child according to the official vaccination schedule?” A version of this item, with an additional description: “Regardless if you are a parent or not,” was previously used by Stojkovic et al. (2017), who adapted it from the scales by Horne et al. (2015) and Opel et al. (2011). Parents will answer this item on a Likert-type scale ranging from “definitely yes” to “definitely not”. Participants' response to this question will be the dependent variable for this study.

##### Vaccination scales

To measure the perceived risk of (not) vaccinating may cause in children and society, we will use the vaccination scale developed by Horne et al. (2015). It is a 5-item scale that measures people's general attitude toward the vaccination (i.e., “Vaccinating healthy children helps to protect others by stopping the spread of diseases,” “I plan to vaccinate my children”). This test has proper psychometric features, including a high internal consistency (α = 0.84), and good predictive validity for past and future vaccination behavior, it has not been used in Europe so far.

Furthermore, the Vaccine Conspiracy Belief scale (Shapiro et al., 2016) will be added at this part. This scale contains 10 items, which examine the belief in the conspiracy theory that different entities try to hide the risk of vaccines. This shows the deception rather than the general attitude people have (Shapiro et al., 2016). An example of this item is: “The government is trying to cover up the link between vaccines and autism.” This scale has a very high level of internal consistency (α = 0.94) and is a good predictor of the willingness of parents to vaccinate their children.

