##### Passive risk-taking

We will measure participants' tendency of passive risk-taking using the Passive Risk-Taking Scale (Keinan and Bereby-Meyer, 2012). While risk mostly occurs during action, passive risk-taking can influence potential losses due to inaction. This test contains three subscales regarding risks that involve resources, medical issues and ethical issues. It has 25 items in total and uses a Likert-type rating scale in which participants will rate how likely they will act according to the statements (i.e., “Get vaccinated for the flu in the winter”). This scale has a high internal validity and reliability (α = 0.82).

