### Proposed analysis

We will use statistical software (Matlab, R) for data analysis. We will analyse samples from each country separately because the differences in terms of language, legal framework in relation to vaccines, demographical characteristics and representativeness make the comparability between the different samples, and thus, their conjugate analysis, difficult (Ember et al., 1998).

For each sample, a factor analysis will be conducted to reduce the number of factors and control for interrelatedness of the variables. Two clusters of variables will be included: demographics (age, education level, number of children, mean age of children), and vaccine-related decision constructs (scores on scales on vaccination, vaccine hesitancy, perceived freedom of the decision, choice overload, actively open-minded thinking, trust toward authorities, availability of relevant information, perceived scientific consensus on vaccination, subjective estimation of percentage of children vaccinated on the country, perceived social consensus on vaccination, risk taking, and elaboration of potential outcomes). We expect the factor structure of each sample to be similar. With the reduced number of factors, a multivariate linear regression analysis will be conducted and the predictive power will be tested. The aforementioned factors will serve as predictors, and the parental intention to vaccinate (“I plan to vaccinate my child in accordance to the official vaccination schedule of my country”) will serve as criterion. All variables mentioned will also be included in a multivariate analysis of variance to see if there are differences between them depending on the level of adherence (total adherence, not completely total adherence, no adherence at all) to the official vaccination schedule of their children. We will test the proposed model of mediation (Figure 1) using regression analysis and compare it to a more complicated model with involvement as an additional factor.

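### Study 1 predicts intention to vaccinate from a set that includes a near-copy of the intention item, so its predictive power will be overstated

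*Protocol article*

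**What the plan says.** All references are to the protocol article, Study 1.

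- *Intention to vaccinate* uses one Likert item, "Would you at this time vaccinate your child according to the official vaccination schedule", and states: "Participants' response to this question will be the dependent variable for this study". It says the item derives from the sources of two instruments, the vaccination scale and the PACV, which are also in the battery.
- *Proposed analysis* gives the regression criterion other words: "I plan to vaccinate my child in accordance to the official vaccination schedule of my country".
- *Vaccination scales* introduces its first instrument as the measure of perceived risk and then describes it thus: "It is a 5-item scale that measures people's general attitude toward the vaccination". One of its two example items is "I plan to vaccinate my children".
- *Proposed analysis* lists the constructs to be factor-analysed, among them "scores on scales on vaccination, vaccine hesitancy, perceived freedom of the decision", followed by trust, perceived consensus and others. The resulting factors are the predictors, and their predictive power is to be tested.
- *Trust toward authorities* and *Perceived consensus and norms* expect more trust and stronger perceived consensus to go with less hesitancy and with more intention. Hesitancy is thus an outcome there. *Anticipated results* names it among the factors that reinforce delay or omission.
- *Perceived consensus and norms* also expects consensus to correlate more strongly with intention than perceived vaccination risk does.

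**The concern.** A statement of intention sits on both sides of the regression. It is one of five items in a predictor score, or 20% of that score if items are equally weighted, and in near-identical words it is the criterion. Part of the explained variance is then intention explaining itself. PACV hesitancy, which includes a Behavior subscale, is a further close proxy for the outcome.

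Two stated aims are affected. The first is predictive power, which the plan sets out to test. The second is identifying which factors, such as trust, consensus and norms, could inform interventions. The consensus-versus-risk hypothesis is affected separately. It is a comparison of correlations and does not pass through the factors.

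**Working it through.** **The plan's own figure.** The minimum of 222 per country rests on an effect size of 0.15 and 20 predictors. Alpha and power are not stated. Reading 0.15 as f² (R² = 0.15/1.15 = 0.130), the noncentral F test with 20 and N − 21 degrees of freedom and λ = 0.15·N needs N = 222 at alpha 0.05 and power 0.95 (power at 222 is 0.951). The figure reproduces, and this point does not affect it.

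**Overlap at scale level.** The article gives α = 0.84 for five items, so the mean inter-item correlation is 0.84/(5 − 4 × 0.84) = 0.84/1.64 = 0.512. The correlation of a k-item sum with the criterion is (sum of item–criterion correlations)/√(k + k(k − 1) × 0.512). The item–criterion correlations are assumed:

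- Other four items at 0.30, without the intention item: 1.20/√10.14 = 0.38, R² = 0.14.
- With the intention item at 0.80 or 0.90: 2.00/√15.24 = 0.51 or 2.10/√15.24 = 0.54, R² = 0.26 or 0.29.
- Other four items at 0.45, intention item at 0.85: R² goes from (1.80/√10.14)² = 0.32 to (2.65/√15.24)² = 0.46.

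The absolute gain is about 0.12 to 0.15 across these cases. The relative gain varies more, from near-doubling to about 1.4-fold.

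**Overlap in the planned factor route.** This was simulated with 200,000 subjects. Trust, consensus and norms correlate 0.3 with one another and feed a common vaccination attitude with weights 0.35, 0.35 and 0.20. Attitude drives intention, four scale items (loadings 0.70 to 0.72) and hesitancy. The fifth scale item is a noisy copy of intention. Four unrelated traits complete the predictor set. R² from regressing intention on two rotated factors:

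| Attitude–intention r | Copy–intention r | Hesitancy–attitude r (absolute) | Neither scale | PACV + 4 items | PACV + 5 items | Gain from the item |
|---|---|---|---|---|---|---|
| 0.50 | 0.60 | 0.70 | 0.109 | 0.211 | 0.279 | 0.068 |
| 0.60 | 0.70 | 0.80 | 0.155 | 0.310 | 0.387 | 0.077 |
| 0.75 | 0.85 | 0.85 | 0.243 | 0.493 | 0.575 | 0.082 |

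With three factors the gain from the item is about 0.09. Both scales together add 0.17 to 0.33 in the two-factor solution (0.279 − 0.109 up to 0.575 − 0.243). Much of that reflects attitudes that really are close to intention. Only the last column is due to the copied item.

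In these runs trust loads about 0.55 on the same factor as the vaccination scale, which loads about 0.84 to 0.89. The regression returns one coefficient for that factor, and trust's share cannot be separated from it.

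**Direction for consensus versus risk.** Adding a copy of intention to the risk score raises the absolute risk–intention correlation and leaves the consensus–intention correlation unchanged. The comparison moves toward risk.

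**The case against.** The strongest defence is the factor analysis, which is meant to handle interrelated variables. A reader might infer that the effects of trust and consensus are adjusted away. With raw scales as regressors that would follow: under the same scenarios trust's standardised coefficient falls from 0.18–0.27 to about 0.01–0.02. But the plan regresses on factors, so the documents do not support that reading. Trust is either merged into a contaminated factor or, if it forms its own, adjusted for one. What remains is that reducing correlation among predictors does nothing about a predictor's overlap with the criterion.

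Hesitancy as a predictor is also a stated hypothesis, and its double role would suit an intermediate variable. A reader might infer that no planned regression has hesitancy as its outcome. That cannot be established, because the mediation model is in Figure 1, which is not shown. This objection stands, and it argues for reporting both models rather than simply deleting PACV.

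The dependent variable in *Intention to vaccinate* is explicit, and the scale item is a near relative of it, not a copy. The duplication is clearest against the wording in *Proposed analysis*. The first pilot may eliminate invalid items, but the article does not make overlap with the criterion a ground for removal.

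A reader might extend the point to the passive risk-taking scale because of its item "Get vaccinated for the flu in the winter". That is one of 25 items, it does not concern the childhood schedule, and the article does not give its scoring direction. It does not support a separate finding.

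Finally, the bias in the consensus comparison runs against the authors' hypothesis. Confirmation would be conservative; the danger is a wrong rejection.

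**Conclusion.** The point holds as criterion contamination. The plan puts a near-copy of the criterion, and a close proxy for it, into the predictor set, and it gives the criterion two wordings. Nothing in the article removes the overlap. Predictive power will be overstated in each country's analysis, and the separate contributions of trust, consensus and norms will not be cleanly readable from this regression.

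The direction follows from the text if the scale is scored as described. The size does not: only the scale's length and α come from the article, and every correlation with intention is assumed. The 0.07 to 0.08 for the item alone is therefore an illustration for a two-factor solution, not an estimate. The bias in the consensus-versus-risk comparison further assumes that the vaccination scale is the risk measure, as *Vaccination scales* suggests.

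**What to change.** 1. Use the item in *Intention to vaccinate* as the single criterion, and align the wording in *Proposed analysis* with it.
2. Drop the intention statement from the vaccination-scale score before the factor analysis, the regression and the consensus-versus-risk comparison. Report the reliability of the remaining four items.
3. Report the intention regression without PACV and the vaccination scale, next to the model that includes them. The hypothesis that hesitancy predicts intention stays testable.
4. Add a parallel regression with PACV as outcome, unless the Figure 1 model already provides it.

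The changes concern scoring and wording only, need no new items, and leave the sample size as it is. The cost is a smaller R-squared and one or two extra models per country.

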##### Vaccine hesitancy

To identify vaccine hesitant parents, we will use Opel et al's. (2011) revised version of Parent Attitudes about Childhood Vaccines (PACV). The measure consists of 15 items, which are divided into three sub-domain scales: Safety and efficacy (α = 0.74), General attitudes (α = 0.84) and Behavior (α = 0.74). The measure has high internal and construct validity, and shows a statistically significant linear association between parents' total score on the 15-item PACV and their child's vaccination status (Opel et al., 2011). To increase the consistency of type of response along the scale and increase the sensitivity of the measure, we transformed some of the multiple-choice items to 7-point Likert type scales, in which each of the extremes represent the options that were included in the original scales. Finally, the item number 15 that referred to parents' trust toward their child's doctor, have been moved to the Trust Toward Authorities Scale (see Appendix 1 for detailed description of the battery).

##### Perceived freedom

The Experience of Freedom Measure (Lau et al., 2015) will be used to measure parents' perceived freedom when making vaccine-related decisions. Participants will rate 4-items (i.e., “I was able to choose what I wanted”) on a Likert-type scale. The measure has good internal consistency (α = 0.82).

##### Choice overload

Lau et al.'s (2015) Choice Overload scale will be used to measure the choice overload within the context of decision-making. Participants will be asked rate the extent to which they agree with 3 statements (i.e., “I felt overwhelmed by the decision”) on a Likert-type scale. This instrument shows good psychometric properties (α = 0.73) relative to the decision on whether to vaccinate their children.

##### Actively open-minded thinking

The Actively Open-Minded Thinking Beliefs (AOT) scale will be used to measure participants' beliefs on whether actively open-minded thinking is a desirable personal feature. The scale was originally developed by Stanovich and West (2007) and revised by Haran et al. (2013). We will use the revised version due to its shorter length (7 items) and adequacy for the general, adult population. Participants will rate how much they agree with given statements on a Likert type scale (i.e., “People should take into consideration evidence that goes against their beliefs”). The scale has been found to correlate with various measures of reflective thinking and good performance.

##### Trust toward authorities scale and sources of information

To measure the perceived credibility and the trust people have toward authorities, Jolley and Douglas' (2014) Trust toward Authorities scale will be used. The scale is built up out of items from previous scales. Participants will rate to what extent they trust corporations, national government, healthcare system, scientists, mainstream media, alternative media, social networks and their child's doctor on a Likert-type scale from strongly mistrust to strongly trust. They will also check all the sources they have used when making a decision about vaccination.

##### Availability of the relevant information

To assess whether parents believe they have enough information to make a solid decision regarding vaccinating their children, we will use one item from the General Health Styles survey by Gust et al. (2005): “I have access to all the information I need to make good decisions about immunization of my children.” Parents will answer on a Likert scale measuring the level of agreement.

##### Exposure to anecdotal cases

This variable will be measured through a single item adapted from the PACV scale by Opel et al. (2011) in a yes/no question format (i.e., “Have you ever heard of anyone who had a bad reaction to a shot?”).

##### Involvement in the vaccination decision

To measure personal involvement on the decision to vaccinate their children, we will include an item asking participants to rate their level of involvement. Additionally, we will ask if any other person is involved in the decision, and how many of them have been. For each of the additional people involved, participants will also be asked to indicate who that person is (the other parent of the child, another family member, a friend or any other person), indicate the gender, and rate the level of involvement of said person.

##### Perceived consensus, norms, and knowledge about vaccination

Additional Likert-type scale items will be used to assess participants' perceived scientific and social consensus about vaccination (i.e., “Is there a consensus among scientist about the safety of the vaccines?” “Is the vaccination an issue in your country?”), norms (i.e., “What do you think is the percentage of vaccinated children in your country?”), and knowledge (e.g., “Is vaccination mandatory in your country?”). The items are based on the items used by Van der Linden (2011) in research dealing with topics of perceived consensus and norms.

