## Introduction

One of the greatest public health challenges today concerns suboptimal vaccine uptake rates. In 2017, measles affected 21,315 people and caused 35 deaths, according to WHO's press release from 19 February 2018. “The surge in measles cases in 2017 included large outbreaks in 15 of the 53 countries in the (European) region. The highest numbers of affected people were reported in Romania (5,562), Italy (5,006), and Ukraine (4,767)” (World Health Organization, 2018). Greece, Germany, Serbia, the United Kingdom, Spain, Bulgaria, and France also experienced large outbreaks (World Health Organization, 2018). This is a result of suboptimal vaccine rates (World Health Organization, 2017a): in many areas, the coverage rates of common vaccines have decreased below 95% that is postulated as the minimum to herd immunity, the effective halting of the spread of measles and other vaccine-preventable diseases.

While some children cannot be vaccinated for medical reasons and in some areas vaccines are not readily available, a growing number of children are not vaccinated or are vaccinated late largely due to their parents' conscious decision (Pearce et al., 2008). The resistance to be vaccinated or to delay vaccinations despite having available vaccinating services, has been dubbed vaccine hesitancy (Luthy et al., 2009; Gowda and Dempsey, 2013; World Health Organization, 2014). Numerous interventions have been introduced to combat vaccine hesitancy, but many are lacking in success (Sadaf et al., 2013; Dubé et al., 2014; Pluviano et al., 2017). To better combat vaccine hesitancy and optimize interventions, factors associated with parents' decisions on vaccination need to be identified and investigated.

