### Methods

#### Design, sample, and procedure

Participants will be parents or primary caregivers of children that are of the recommended age to receive vaccinations from their corresponding countries across Europe and Asia (i.e., Finland, Germany, Hong Kong, the Netherlands, Serbia, Slovenia, and Spain). Participants must be (a) over 18 years old, and (b) a parent or care taker of at least one child under the age of 12 years (Salmon et al., 2005; Jones et al., 2012).

The sample size will be a minimum of 222 participants per country, based on a power analysis for an effect size of 0.15, and 20 predictors in a linear multiple regression model. The final sample size will not have a difference greater than 10% between each country. To make sure that there aren't any significant differences between the sample sizes of the different countries, if the sample of any country exceeds 10% of the mean, some participants will be randomly discarded until the criterion is met.

The questionnaire is programmed in JavaScript and will be administered online. To take part in the study, participants will need an electronic device with access to internet. The link with an unbiased invitation letter will be posted on different social media platforms, forums and websites, targeting a wide range of parents from the entire vaccine-hesitancy spectrum. Once the link is opened, participants will first be given a brief introduction of the study. Participants will then read and sign an informed consent, which states they are able to halt and withdraw from the study at any moment without providing a reason, and that they agree for their anonymized data to be analyzed for future publications. Participants will be asked to compose a unique identification code (consisting of their parents' initials, and month of birth), which will be used to identify their data if they decide to withdraw their data after completing the study. After that, participants will be asked to provide their demographic information and complete a battery of vaccination- and decision-making-related questions, with a total of 115 items (the complete battery is in Appendix 1). Participants will be able to leave items unanswered. The study will take ~25 min to complete, but will vary depending on participants' speed of responding. This procedure was ethically approved by the Institutional Review Board of the Faculty of Philosophy at the University of Belgrade.

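### Study 1 records parents' estimate of the percentage of vaccinated children on a 7-point Likert-type scale; a 0 to 100 number would avoid a coarsening that is small to moderate depending on how answers cluster (minor)

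*Protocol article*

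**What the plan says.** Three parts of the Study 1 text of the protocol article bear on this item.

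- **Perceived consensus, norms, and knowledge about vaccination.** The section opens with "Additional Likert-type scale items will be used to assess" perceived consensus, norms and knowledge. Its example for norms is "What do you think is the percentage of vaccinated children in your country".
- **Choice of measures.** The general rule is that "all continuous variables will be measured with 7-point Likert-type scales". The reasons given are homogeneous measurement across constructs, the format of most source instruments, and the view that the number of scale points does not affect metric properties. The same section says that country-level data will be collected, "such as the percentage of vaccinated children in a country".
- **Proposed analysis (Study 1).** The "subjective estimation of percentage of children vaccinated on the country" is one of the vaccine-related variables entered in the factor analysis. The resulting factors then predict intention to vaccinate, separately in each country.

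Nothing in the article exempts the percentage item from the 7-point rule. Its response options are not shown: the section on design, sample and procedure says that "the complete battery is in Appendix 1".

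**The concern.** The reasons given for a uniform 7-point format suit ratings of agreement or trust, which have no unit of their own. The percentage question does have a unit. A parent can answer it as a number, and coding that number into seven categories discards information that cannot be recovered later.

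The loss is uneven. If most parents think that the great majority of children are vaccinated, many answers fall into the top one or two codes and the item has little variance left. Its correlation with intention, its loading in the factor analysis and its part in the planned norms-by-consensus moderation would then be weakened by the response format alone. A weak result could be read as norms mattering little.

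**Working it through.** The plan gives no figure on this point to reproduce, so the check is category arithmetic followed by a simulation under stated assumptions.

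**Inputs from the document**
- Seven response points (Choice of measures).
- A percentage question among the Likert-type items (Perceived consensus, norms, and knowledge about vaccination).
- Use as a quantitative variable within each country (Proposed analysis, Study 1).

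**Inputs not in the document, hence assumed**
- The category limits.
- The distribution of parents' estimates.

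**Step 1: width of the top category**
- Coding A, seven equal bins over 0 to 100%: width 100/7 = 14.3 points. The top bin runs from 100 − 14.3 = 85.7% to 100%.
- Coding B, rounding to seven equally spaced points (0, 16.7, …, 100): spacing 100/6 = 16.7 points. The top code runs from 100 − 16.7/2 = 91.7% to 100%.
- Other limits move this edge. With seven equal bins starting at 30, 50, 60, 65, 70 or 80%, the top bin starts at 90.0, 92.9, 94.3, 95.0, 95.7 or 97.1%.

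**Step 2: information kept**

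Underlying estimates are drawn from a beta distribution on 0 to 100% with mean m and SD s (as proportions): k = m(1 − m)/s² − 1, a = mk, b = (1 − m)k. Each draw is coded 1 to 7. The results are the share in the top code and the correlation r of the code with the underlying percentage.

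| Mean, SD of estimates | A: top share | A: r | B: top share | B: r |
|---|---|---|---|---|
| 80, 15 | 44% | 0.96 | 26% | 0.95 |
| 85, 12 | 57% | 0.94 | 36% | 0.94 |
| 90, 8 | 76% | 0.88 | 52% | 0.89 |
| 93, 5 | 91% | 0.72 | 68% | 0.83 |

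**Step 3: effect on the association with intention**

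If intention is linearly related to the underlying estimate, and the code carries no further information about intention, then

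corr(code, intention) ≈ r × corr(estimate, intention).

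The proportional loss is 1 − r:
- wide spread (first two rows): about 4 to 6%;
- clustered at 90, SD 8: 1 − 0.89 = 11% to 1 − 0.88 = 12%;
- clustered at 93, SD 5: 1 − 0.83 = 17% to 1 − 0.72 = 28%.

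Codings that place more categories at the upper end lose less. With seven bins starting at 50%, the loss is at most 8% in all four scenarios.

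**The case against.** **The format is not fully established.** The response options are in the appendix, and both sentences relied on are summaries. The 7-point rule cannot be literal for every continuous variable, since age and number of children are also analysed. If the anchors are verbal, there are no percentage bins and the table above does not apply. This stands as a limit on the size. It does not remove the point, because unlike age this item is expressly listed among the Likert-type items, and a verbal scale would be coarser still as a record of a percentage.

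**The loss may be small.** Parents are recruited across the whole hesitancy spectrum, so estimates may spread widely, and the loss is then 4 to 6%. The item is one of many inputs to a factor analysis. The first pilot also examines how items function and could reveal answers piled in one category. All of this stands and keeps the point minor.

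**Stronger readings that a reader might infer, and that the document does not support**
- *That true coverage lies in the top category.* No study country's coverage is given. The Introduction says only that in many areas "the coverage rates of common vaccines have decreased below 95% that is postulated as the minimum to herd immunity". The 86% edge comes from an assumed coding, and the item records beliefs, not coverage.
- *That beliefs above and below 95% can never be told apart.* This follows for categories spread evenly over 0 to 100%, but not for every coding: bins starting at 65% or higher put a limit at or above 95%. Nor is 95% an analysis cut-off; it is background, and no hypothesis classifies parents against it.
- *That the format breaks a planned comparison of perceived with actual coverage.* The perceived-versus-actual gap behind the Gateway Belief argument, in the section on perceived consensus and norms, concerns scientific consensus, which has its own item. No comparison of estimated with national coverage is planned. Within a country the national figure is a constant, so subtracting it changes no correlation, loading or slope.

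**Conclusion.** The point holds as a minor, conditional one. As written, the article puts a percentage estimate on a 7-point Likert-type scale and then analyses it as a quantity, so resolution is given up at collection without need.

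The size depends on two things the article does not give: the category limits and the spread of parents' answers. With categories spread evenly over 0 to 100% and beta-distributed estimates, the coded score correlates 0.94 to 0.96 with the estimate when answers spread widely and 0.72 to 0.89 when they cluster near 90% or above. The norm's association with intention is attenuated by about 4 to 6% in the first case and 11 to 28% in the second. Limits concentrated at the upper end would reduce this. No effect on a main conclusion of Study 1 is shown.

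**What to change.** State that this item is exempt from the 7-point rule. Collect it as a whole number from 0 to 100, by numeric box or slider, and standardise it before it enters the Study 1 factor analysis and regression.

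Comparing parents' estimates with the national figure that is already to be collected can be added as a descriptive summary. It is optional and leaves the within-country regressions unchanged.

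The cost is one different input field in an online questionnaire. The downside is one item whose response format differs from the rest of the battery.
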